### Participants

Eligibility criteria includes: Adult (>18 years) having proven coronary artery disease and completion of a Phase 2 cardiac rehabilitation program within the past 9 months; available to attend two yoga sessions per week and complete a simplified self-administered yoga program once a week for the duration of the study; not currently or previous engaged in a yoga program (>3 yoga session); no acute or chronic medical conditions which would make yoga potentially hazardous; ability to communicate in English; willingness and cognitive ability to provide written informed consent. Should the participant have any of the following conditions they will be excluded from the trial: pacemakers or implanted defibrillators, pregnancy; end stage congestive heart failure; permanent bed-bound status; unstable abdominal, thoracic or cerebral aneurysm; acute myocarditis, pericarditis, pulmonary embolus or pulmonary infarction; severe cognitive deficits (MMSE < 21); previous or current psychological disorders that are not associated with depression or anxiety.

### Randomization

Participants will be randomized via computer-generated randomly permuted blocks into interventional group or control group. The randomization assignments will be prepared by a National Institute of Complementary Medicine (NICM) Research Program Coordinator who is external to the research team. Group assignment will be delivered to participants in sealed envelopes once the participant is screened and fully enrolled.

### Intervention

#### Experimental group

Participants randomised to the yoga therapy group will receive two supervised yoga sessions per week for a period of 12 weeks. They will also be provided with a simplified take-home yoga program, which they will be instructed to practice once per week. The yoga sessions will be group-based and led by an experienced yoga instructor from Yoga Synergy Pty Ltd (Sydney, Australia) [46]. These sessions will run twice per week for approximately one hour per session (details of yoga sequence and time requirements outlined in Table 1). The hatha yoga program will be similar to that used by the research team in a previous study [45] and will involve teaching beginner students safely and progressively over 12 weeks incorporating *asanas* (poses and postures), *pranayama* (breathing control) and *savasana* (meditation). At the start of each session, a series of introductory movements designed to warm-up the extremities, large joints and spine (*itkata vinyasa* and *utkata danda nadi vinyasa*) will be conducted before moving into a salute to the moon (*candra namaskar*). This will be followed by standing postures which are linked to one another to warm up the body whilst stretching and strengthening the muscles (*trikonasa*, *parsvakona*, *gadja hasta padottana*, *gadja baddha padottana*, *parsvottonasa*, *eka pada*, *virabhadra*). Following this, a series of floor postures which are also linked together will be conducted and include: forward bends, twists, hip opening, back arches, and back arch releases. As participants become more competent with training, an inversion (shoulderstand) is added to help calm and restore the body and nervous system. This is followed by a series of neck and spine releases to ensure participant safety. Participants then sat on the floor and engaged in breathing exercises (pranayama) and then supine meditation/relaxation (*savasana*). All postures and exercises are comprised of a simple and more challenging variant to allow difficulty to be scalable within the yoga program in relation to participant ability and capacity.

**Table 1 Tab1:** **Yoga routine**

Introductory section	
5 Minutes	Utkata Vinyasa
	Utkata Danda Nadi Vinyasa
	Candra Namaskar
	Surya Namaskar
Standing Postures	
10 Minutes	Trikonasa Vinyasa
	Parsvakona Vinyasa
	Gadja Hasta Padottana Vinyasa
	Gadja Baddha Padottana Vinyasa
	Parsvottonasa Vinyasa
	Eka Pada Vinyasa
	Virabhadra Vinyasa
Floor Postures	
10 Minutes	Pashima Vinyasa
	Janu Sirsa Vinyasa
	Maricy Vinyasa
	Baddha Kona Vinyasa
	Pada Sirsa Preparation Vinyasa
Back Bending Sequence	
5 Minutes	Adho Viparita Vinyasa
	Adho Viparita Vinyasa
	Urdhava Dhanura Vinyasa
Back Bend Releasing Sequence	
5 Minutes	Urdhva Dhanura Releasing Vinyasa
	Hasta Vinyasa
Shoulderstand, Releasing Postures & Finishing Postures	
10 Minutes	Sarvangasana Vinyasa
	Viparita Mudra Vinyasa
	Padma Vinyasa
Pranayam Meditation & Relaxation	
15 Minutes	Nadi Padma Namaskar
	Nadi Sodhana Pranayama
	Savaasana

#### Control group

Participants randomised to the wait list control group will receive no instructions about yoga practice for the 16 week trial period (12 week intervention +4 week follow up). Upon their completion of the trial, wait list participants will be given the opportunity to participate within the yoga program.

### Outcomes

Participants will be restricted from consuming caffeine 4 hours prior to and alcohol 24 hours prior to each of the four testing sessions (baseline, mid-intervention, post-intervention, follow-up). This includes caffeinated products such as caffeine tablets (No-Doz, etc.) as well as caffeinated drinks.

### Psychological outcomes

#### Depression Anxiety Stress Scales (DASS)

The DASS is a set of three self-reported scales designed to assess the negative emotional states of depression, anxiety and stress. Each of the three DASS sub-scales contains 14 items, divided into subscales of 2–5 items with similar content. The DASS has been employed in a number of studies in cardiac populations and has been shown to have good test-retest reliability coefficients for all scales [53]. The DASS scale was found to show better discrimination when assessed in comparison to a well-established coronary prone behavioural pattern scale such as the Framingham Scale in a group of Myocardial Infarction (MI) and matched control patients [54]. While not as widely used as other questionnaires of anxiety and depression such as the State Trait Anxiety Inventory, Beck Depression Inventory or Beck Anxiety Inventory, the DASS shows greater discriminant validity in regards to these psychosocial factors [11]. Participants will be asked to use 4-point severity/frequency scales to rate the extent to which they have experienced each state over the past week. Overall DASS scores will be calculated and presented for statistical analysis.

#### Short Form 36 version 2 (SF36v2)

Short Form 36 is a psychometrically robust and clinically credible 36–item questionnaire that is designed to assess health related quality of life across diverse medical and psychiatric groups [55, 56]. It has also been shown to be a valid and reliable instrument for assessing physical and mental health status of cardiac patients and that CVD is associated with reductions in health-related QoL [57]. The SF36v2 organises the 36 items into eight components and presented on a percentage scale (0–100) and T-score. These eight components will be combined into two summary measures to provide overall estimates of physical and mental health. SF36v2 will be presented to participant as either a paper based questionnaire or as an electronic survey using Evado clinical trial software (Evado, Melbourne, Australia).

#### Cardiovascular measurements

Heart Rate and Blood Pressure: All blood pressure and heart rate measurements will be calculated using an automatic sphygmomanometer, designed for professional use (Omron, Sydney, Australia). Brachial arterial blood pressure will be taken following a 5 minute rest period. This will be done with an automatic sphygmomanometer whilst the participant is sitting comfortably.

Heart Rate Variability (HRV): HRV has been extensively used to assess vagal function and the associations between autonomic imbalance and disease morbidity and mortality [58]. To date, there is a large body of evidence indicating that HRV is an independent predictor of CVD morbidity and mortality in both high and low risk populations [59–62]. Whilst large population studies have highlighted this association as early as the 1980s, recent research has strongly suggests that negative affective states may significantly impacts on HRV, disease and poor health [63, 64]. Time and frequency domains measurements of HRV have been successfully used to index vagal activity and although there is debate regarding the reflection of Parasympathetic Nervous System (PNS) and/or Sympathetic Nervous System (SNS) influence of low frequency power, high frequency power has been shown to primarily reflect PNS activity with consensus amongst numerous studies is that lower index values of vagal function are associated with disease morbidity and mortality [65]. Three electrocardiogram (ECG) electrode pads will then be placed onto the participant’s upper left and upper right chest as well the lower left side of the torso. Participants will be asked to lay supine for 10 minutes during which the SphygmoCor system (AtCor Medical, Sydney, Australia) will capture data for HRV calculation. Data from both time (standard deviation of R to R intervals and root mean square successive differences) and frequency (high and low frequency spectral power and ratios) domain variables will be collected and analysed. This will provide indices that reflect the input to the heart from the two major branches of autonomic nervous system, the SNS and PNS.

Pulse Wave Velocity (PWV): Pulse Wave Velocity is generally accepted as the simplest, non-invasive, robust and reproducible method of determining arterial stiffness [66]. Research indicates it has independent predictive value for cardiovascular mortality and morbidity in a wide range of pathological and general populations [67–70]. Non-invasive PWV has been validated against invasive aortic PWV (correlation coefficient = 0.70) with suprasternal notch-femoral minus carotid-suprasternal notch distance showing the best agreement with invasive data [71]. While the participant is still supine, an ECG-femoral and carotid tonometric procedure will also be conducted. PWV procedure will be conducted in accordance to with recommendations outlined in the *Expert Consensus Document on Arterial Stiffness*
[66]. Travel distance will be calculated by subtracting the carotid artery to suprasternal notch distance from the suprasternal notch to femoral artery. A single high fidelity applanation tonometer will then be placed over carotid and femoral arteries and data will be acquired for PWV. Travel time between the two arterial sites will be calculated as the difference between R-waves and the footpoints at their respective sites [71]. Footprint of the pressure wave at both sites will be automatically assessed using the intersecting-tangent method [71]. Calculations will be completed using SphygmoCor Cardiovascular Management Software (AtCor Medical, Sydney, Australia).

Carotid Intima Media Thickness (CIMT): Measurement of CIMT with B-mode ultrasound is a sensitive, non-invasive and reproducible technique for both identification and quantification of subclinical vascular disease and for evaluating CVD risk [72]. Imaging of the carotid artery to identify areas of increased thickness and non-occlusive atherosclerotic plaque which represents early stages of arterial injury and atherosclerosis has increasingly being used as a surrogate cardiovascular endpoint in a number of clinical trials [73]. Whilst there are numerous reviews and studies providing evidence that CIMT is strongly related to CVD incidents and that it is a well validated research tool , variations in methodology and sparse clinical data has prevented widespread adoption of this technique for routine assessment in clinical settings [74]. As a result, numerous guideline and consensus statements have been produced in an attempt to standardise CIMT procedures for research and clinical use. CIMT procedures in this study will be conducted in accordance with the *Mannheim Carotid Intima-Media Thickness Consensus (2004–2006)*
[73]. The participant will be asked to lie in a supine position with their head tilted to the side. High resolution B-mode carotid ultrasonography will be performed using a 13Mhz linear-array transducer on a GE Vivid I ultrasound system (GE Medical, Sydney, Australia). Pre-processing configurations will be held constant during all examinations. The gain is to be adjusted so that the less dense arterial wall interface should be just visible and the image should clear show both near and far vessel walls. The Common Carotid Artery (CCA) will be insonated longitudinally and perpendicular to the vessel wall. Measurements are to be taken from the far wall of the CCA within 10 cm from the carotid bifurcation and of a minimal measurement length of 10 mm. IMT to be defined as the distance between the luminal-endothelial interface and the junction between the media and adventitia. Mean values of at least 10 measurements at systole are to be used for measurement. Image sets will be assessed for clarity and automatic edge tracking software known as EchoPak (GE Medical, Sydney, Australia) to be used offline to determine averaged mean and maximal IMT values and adventitia to adventitia diameter.

#### Cognitive function

Computerised Mental Performance Assessment System (COMPASS): The Computerised Mental Performance Assessment System (COMPASS) features a number of computerised cognitive tasks designed to test various aspects of mental function. The COMPASS test battery has been used in numerous cognitive studies and has been shown to be sensitive to changes in a number of cognitive domains [75–77]. The system employs a range of similarly validated cognitive tasks seen in computerised test suites such as the Cognitive Drug Research computerised assessment system however COMPASS is a purposely designed software application allowing for greater flexibility in choice of tasks and delivery of randomly generated parallel versions of standard cognitive assessment tasks [78]. Data from alternate forms of each task presented during testing sessions will be automatically captured by the COMPASS software.

#### Biochemistry markers

Low Density Lipoproteins (LDL), High Density Lipoproteins (HDL) and Triglycerides: Lipid levels, such as low High Density Lipoprotein (HDL) and high Low Density Lipoprotein (LDL) and triglyceride levels have been shown to be associated with increased risk of CVD [79]. Whilst the initiation of atherosclerosis has been long debated, mounting evidence suggests that LDLs interact with arterial walls allowing for prolonged exposure to local enzymes, both oxidative and non-, leading to modifications of lipoproteins and their constituents [80]. These modified lipoproteins have been suggested to play a role in inflammatory reactions that accelerate lesion development [81]. In contrast, research into HDLs highlight their functionality as being potentially highly vaso-protective in inhibiting endothelial apoptosis, maintain vaso-reactivity, contributing to endothelium repair and reducing adhesion molecule expression [82]. All of these actions may attenuate key processes of atherosclerotic plaque formation. In addition, population studies that provide evidence of associations between low HDLs and CVD risk are strong and consistent [79, 83]. Lipid profiles will be determined before and after the intervention at weeks 0 and 12. Participants will be sent to have blood samples taken and pathology testing conducted by a reputable pathology collection centre.

Glucose: Similarly to cholesterol, plasma glucose levels have been observed to be a continuous risk factor for CVD with diabetic patients exhibiting at least a 2-fold increase in risk [84]. However as traditional glucose cut off levels were chosen to identify diabetes mellitus and not increased CVD risk, people with elevated but below diabetic glucose concentrations still represent increased risk which has been highlighted in several large population studies [85–87]. Glucose profiles will be determined before and after the intervention at weeks 0 and 12. Participants will be sent to have blood samples taken and pathology testing conducted by a reputable pathology collection centre.

C-reactive protein (CRP): C-Reactive protein (CRP) was initially used as a non-specific biomarker for inflammatory processes however has become a powerful independent modifiable predictor of CVD in various clinical and non-clinical populations [88, 89]. The Centre for Disease Control and Prevention and the American Heart Association have issued a Class IIa recommendation that screening of CRP be a routine part of a patient’s global cardiovascular risk assessment and in primary prevention, CRP adds prognostic value to all levels of Framingham risk [90]. In addition to this, CRP was found to be a stronger predictor of CVD incidences that low density lipid levels [91]. CRP will be determined before and after the intervention at weeks 0 and 12. Participants will be sent to have blood samples taken and pathology testing conducted by a reputable pathology collection centre.

#### Participant diary

Participants will also be asked to complete a weekly diary documenting drastic changes in diet, commencement or cessation of negative behaviours such as alcohol consumption and smoking, number of hours spent exercising, changes in medication, significant positive or negative life events, adverse events, and compliance to yoga program. These behaviours will be monitored by open-ended questions to be completed weekly. This data will be presented for a descriptive synthesis only with compliance to yoga sessions and adverse events, coded into a binary yes/no format, to be considered for inclusion in analysis of covariance (ANCOVA) models as covariates.

#### Safety and adherence

In addition to data collected from participant diaries, each assessment visit will detail any information pertaining to adverse events and yoga session compliance will be monitored through class attendance. As stated previously, this data will be included for ANCOVA models as covariates.

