### Statistical analysis

Analysis is to be performed using the R statistics package (version 3.1.1). All data will be inspected visually and statistically for normality (skewness and kurtosis between -1 and +1). Analysis of variance (ANOVA) and chi-squared tests of independence will be used to check for any differences between groups at study entry, any differences found here will be controlled for in that outcome analysis. Outcome analysis will take the form of ANCOVAs to detect changes between the experimental and control groups at post- treatment while controlling for baseline values and other possible confounders such as age, gender, time since cardiac incident, time since phase-2 CR completion and current exercise regimen or phase-3 CR participation. Multiple imputations will be used to impute missing data for participants with less than 10% missing data. An intention to treat analysis in which all missing data will be managed with multiple imputations will be conducted along with a separate per protocol analysis in which those with greater than 10% missing data or less than 60% yoga session attendance will be excluded. A p-value of less than 0.05 will be considered statistically significant.

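### The protocol puts yoga compliance and adverse events, both arising after randomisation, into the ANCOVA (firmly in one section, tentatively in another); with compliance adjusted for, the group coefficient no longer estimates the effect of assignment

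*Protocol article*

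**What the plan says.** Three sections of the protocol article bear on this.

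- **Participant diary.** Diary data are for description only, with one exception: "compliance to yoga sessions and adverse events, coded into a binary yes/no format, to be considered for inclusion in analysis of covariance (ANCOVA) models". This is tentative.
- **Safety and adherence.** The data sources are widened: "each assessment visit will detail any information pertaining to adverse events and yoga session compliance will be monitored through class attendance". The next sentence is firm: "As stated previously, this data will be included for ANCOVA models as covariates". It presents itself as a restatement of the diary section but goes further than that section does.
- **Statistical analysis.** ANCOVA is the planned model for the outcomes: "Outcome analysis will take the form of ANCOVAs to detect changes between the experimental and control groups at post- treatment while controlling for baseline values". Baseline values are joined by "other possible confounders such as age, gender, time since cardiac incident, time since phase-2 CR completion and current exercise regimen or phase-3 CR participation". That list is given by example, so it neither names compliance and adverse events nor rules them out. The same section promises both analysis sets: "An intention to treat analysis in which all missing data will be managed with multiple imputations will be conducted along with a separate per protocol". The per-protocol set excludes, among others, participants with under 60% yoga attendance.

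The Control group section says that wait-list participants get no yoga instruction during the 16 weeks. No section confines the compliance and adverse-event covariates to a secondary or exploratory model.

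**The concern.** Randomisation protects the comparison of everyone assigned to yoga with everyone assigned to the wait list. A covariate measured before randomisation leaves that comparison intact and usually sharpens it. A covariate that assignment itself influences does not.

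Yoga compliance is an extreme case. Controls have no classes to attend, so a positive value exists only in the yoga arm. The indicator overlaps heavily with the arm variable and lies on the path by which yoga would work. Whatever benefit comes through attendance is credited to the compliance coefficient, and the group coefficient is left to describe yoga participants who did not comply. These people are self-selected, so even that residual contrast is not randomised.

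At stake is the main result on the DASS. The reported group effect could vanish when yoga works, or appear when it does not. Adverse events raise a milder form of the same problem: yoga may change their frequency, and adjusting for them would then remove or distort part of the effect.

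**Working it through.** **The plan's own figure.** The sample-size section gives 112 participants for a standardised mean difference of 0.69 and states no power. With two-sided alpha 0.05 and 95% power, the normal formula gives 2(1.960 + 1.645)²/0.69² = 54.6, so 55 per arm and 110 in total; the t-distribution gives 112. At 80% and 90% power the normal-formula totals are 66 and 90. So 112 reproduces if 95% power is assumed. I use 56 per arm below. The point itself does not depend on the sample size.

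**Inputs.** From the protocol: difference 0.69, 112 analysed, alpha 0.05 (sidedness not stated, two-sided assumed), no yoga for controls. Assumed, because the protocol gives none: compliance c (70% unless stated), a binary indicator coded no for every control, baseline–outcome correlation r of 0.5 to 0.6, and the link between attendance and prognosis.

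**Step 1. What the coefficient estimates.** With arm and a compliance indicator that is zero in all controls, there are three cells: controls, non-compliant yoga and compliant yoga. The group coefficient is the baseline-adjusted mean of non-compliant yoga minus that of controls. This is algebra and holds for any c strictly between 0 and 1. At c = 0.7 it rests on 56 × 0.3 ≈ 17 yoga participants against 56 controls.

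**Step 2. Precision.** The variance is proportional to 2/n without the indicator and to 1/[n(1 − c)] + 1/n with it. The ratio is (1/(1 − c) + 1)/2:

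| c | ratio |
|---|---|
| 60% | 1.75 |
| 70% | 2.17 |
| 80% | 3.0 |
| 90% | 5.5 |

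**Step 3. Benefit only in attenders.** Each complier gains 0.69/0.7 = 0.99 SD, which averages 0.69 over the arm. In simulation the group coefficient is −0.69 without the indicator (significant in about 97–99% of trials) and 0.00 with it (significant in about 5%).

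**Step 4. Equal benefit in all yoga participants.** The coefficient stays at 0.69 but its standard error grows. Without the indicator, SE = √(1 − r²) × √(2/56).

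- r = 0.5: SE 0.164, power 99%. With the indicator, 0.164 × √2.17 = 0.241 and 0.69/0.241 = 2.86; power 81%.
- r = 0.6: SE 0.151, power over 99%. With the indicator, 0.151 × √2.17 = 0.223 and 0.69/0.223 = 3.10; power 87%.

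Simulation that lets the number of compliers vary gives slightly lower power with the indicator (79% at r = 0.5).

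**Step 5. No true effect, attendance related to prognosis.** Let the latent tendency to attend correlate with the part of the outcome not explained by baseline, at strength k. The mean shift among the 30% who do not comply is k × 0.348/0.3, where 0.348 is the normal density at the 30th percentile. At r = 0.5 this is scaled by √0.75 = 0.866:

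- k = 0.3: bias 0.866 × 0.3 × 1.159 = 0.30 SD; simulated type I error about 24%.
- k = 0.5: bias 0.866 × 0.5 × 1.159 = 0.50 SD; simulated type I error about 56%.

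Without the indicator, type I error is about 5% in both. If better-prognosis participants attend more, yoga looks harmful; if worse-prognosis participants attend more, it looks beneficial.

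**Adverse events** were not simulated.

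**The case against.** **Inclusion is not settled.** The firm sentence points back to a tentative one, and the statistical section lists neither variable. That stands: the documents disagree, and a reader should not infer that inclusion is definite throughout. But the tentative reading is no remedy, because it leaves a post-randomisation covariate to be chosen later, with no criterion given for choosing it.

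**The sizes are driven by assumptions.** True. The protocol gives no compliance rate, no baseline correlation and no cut-off for a compliant participant. The 0.00 in step 3 follows directly from supposing that only attenders benefit. Step 1 needs none of these beyond the binary coding.

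**Larger power losses can be computed.** An unadjusted t-test at 70% compliance falls from 95% to 69%. The planned model adjusts for baseline, so the 81–87% figures are the relevant ones.

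**Intention to treat is not violated.** A reader might say the covariates contradict the promised intention-to-treat analysis. They remove nobody from that analysis set. What is lost is the interpretation of the coefficient as the effect of assignment.

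**Adverse events are weaker ground.** An event can occur in either arm, so the near-collinearity of compliance is absent. That stands, and this limb is secondary.

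**Current exercise and phase-3 rehabilitation.** A reader might infer that these covariates share the fault. The documents do not support this. They are listed beside age, gender and time since rehabilitation, where a study-entry value is the natural reading, and the weekly diary's exercise hours are reserved for description.

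**Conclusion.** The concern holds for yoga compliance and should be fixed before analysis. One section commits to the covariate, another only entertains it, and none limits it to a secondary model. If it enters the outcome ANCOVA as a binary indicator, the group coefficient contrasts non-compliant yoga participants with all controls, whatever the true effect.

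The consequence ranges from a loss of power (99% to 81–87% at 70% compliance, if benefit does not depend on attendance), through complete loss of a real effect (if benefit comes only through attendance), to a false effect of 0.3 to 0.5 SD (if attendance tracks prognosis). These figures are illustrations under the stated assumptions, not predictions for this trial. For adverse events the conclusion is only that assignment may affect them, so they do not belong in the primary adjustment; the bias has no figure.

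**What to change.** 1. Delete the covariate sentence under Safety and adherence and the matching ANCOVA clause under Participant diary, so that the three sections agree.
2. In Statistical analysis, restrict the intention-to-treat ANCOVA to arm, baseline score and covariates measured at baseline.
3. Use attendance only in the per-protocol analysis already planned. A complier-average causal effect analysis could be added, but is optional and not needed to cure the fault.
4. Report adverse events by arm as a safety outcome.

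The cost is a change of wording. No new data, visits or participants are needed.
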